## Methods

### Study Design

The study includes 2 recruitment phases. The first phase concerns a single case experimental design (SCED) study (substudy 1) with a total of 12 patients (6 children and 6 adolescents, respectively). The second phase concerns an open pilot study on cognitive biases and interoceptive accuracy (substudy 2) with a total of 60 patients (30 children and 30 adolescents, respectively).

Consequently, a total of 72 children and adolescents, along with a corresponding number of parents, will undergo ICBT for FAPDs throughout the entire study. Parental distress and illness worries will be assessed before, during, and after the treatment in all included parents (substudy 3; Figure 1).

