#### Design and Content of Treatment

The 4 distinct ICBT programs used in this study are targeted children (8-12 years), adolescents (13-17 years), and the parents of each group, respectively. The treatment lasts for 10 weeks and consists of 10 modules for children, adolescents, and parents of children (with a new module every week) and 5 modules for parents of adolescents (with a new module every other week). An overview of treatment content can be seen in Table 1. The programs include sections with videos, exercises, and quizzes designed to actively engage the child or adolescent in the treatment. Psychoeducation regarding FAPDs, detection of avoidance behavior, a brief mindfulness exercise called “SOL (Stop, observe, let go)” and graded repeated exposure exercises comprise some of the central components covered in the programs for both children and adolescents. The first modules of treatment introduce the above-mentioned concepts whereas later modules focus on repeated exposures. The purpose of “SOL” is Stopping, Observing how the stomach feels, and Letting go of the focus on the stomach and continuing with the activity. The parental programs emphasize supporting their child or adolescent’s exposure, decreasing attention to their child or adolescent’s abdominal symptoms, and prioritizing shared positive activities. Each module ends with planning of the homework assignments which are evaluated first thing in the next module.

**Table 1 table1:** Overview of the content of treatment for each module.

Module	Children (8-12 years)	Parents	Adolescents (13-17 years)	Parents
1	Introduction to the treatment format Psychoeducation on FAPDs^a^ (video) Mapping “stomach behaviors” (control, avoidance, safety) Setting treatment goals Homework: Self-monitoring	Introduction to the treatment format Positive attention Focus shift Mapping common parental behaviors Handling personal frustrations Homework: Focus shift, breaks, involving peers	Introduction to the treatment format Psychoeducation on FAPDs (video) Setting treatment goals Homework: self-monitoring	Introduction to the treatment format Focus on positive attention and shared moments Mapping common parental behaviors Homework: Shared positive moments

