#### Measures of Parental Factors and Child Treatment Effects (Substudy 3)

To assess how parental distress, illness worry, and behavior impact the child’s overall treatment effects in various domains and treatment adherence, all participating parents and children or adolescents in the ICBT programs will answer extensive questionnaires before assessment (T1: baseline), halfway through treatment (T2: mid-treatment), at end of treatment (T3: end of treatment), and 3 months after the end of treatment (T4: follow-up; Figure 1). Furthermore, the number of completed treatment modules will be obtained from the treatment web page after the end of treatment. The specific measures to be used are shown in Table 2 and described subsequently.

**Table 2 table2:** Overview of questionnaires in substudy 3.

Outcome			Instrument	Time points and respondents^a^			
				T1	T2	T3	T4

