### Sample Sizes

According to research design standards [65], a minimum of 3 replications are recommended in a SCED study (substudy 1). However, to achieve sufficient power for randomization tests, a higher number of potential randomizations is recommended [66]. The number of randomizations is influenced by both the number of participants and the number of possible starting points; hence, guided by Levin et al [67], we chose 6 participants in each group.

For substudy 2, we based our power analysis on potential differences in cognitive bias and interoception between cases and healthy controls on a previous similar study on cognitive bias in children and adolescents [40] and studies on interoceptive accuracy in adults with functional disorders [68-69]. Based on these study findings, calculations show that in order to detect a minimum effect size of 0.5 (Cohen *d*), 60 patients and 100 healthy controls are required for the cognitive bias outcome, and a minimum of 51 patients and 51 healthy controls for the interoception outcome to achieve 80% power at an α level of .05. The subsequent analysis of the possible impact of treatment on these 2 factors is more explorative and therefore no a priori power calculation is provided. The same concerns the last study on parental factors (substudy 3) as possible effect moderators. However, here the sample size is the largest possible, comprised of parents from substudies 1 and 2.

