### Data Analyses

In substudy 1, visual inspection analyses will be applied to demonstrate the effect of the intervention on all outcomes [71]. In addition, within-case effect size measurements will be calculated using Tau-U [72] and between-case effect sizes will be determined using hierarchical linear regression models to account for the serial dependency of data [73]. A randomization test will be applied to test differences in means for the baseline versus treatment, and baseline versus follow-up periods, respectively [74].

In substudy 2, participants’ descriptions reported in the recall phase of the BY-GIS task will be coded to their corresponding word or picture and category presented in the encoding phase (eg, picture-description “children and cake” coded as the birthday picture within the fun category). Coding for the first 20% of participants will be conducted by 2 independent raters ([name] and [name]). If the consensus rating exceeds 90%, 1 rater will code the remaining cases independently. A third and experienced rater ([name]) may be consulted to resolve potential disagreements. Baseline data will be analyzed descriptively and compared with (1) data from a healthy control group who performed the same experimental test [38], and (2) end-of-treatment data, exploring potential differences in the outcomes from the encoding, recall, and recognition phases using *t* tests or nonparametric tests, depending on data variability in the samples.

Baseline measures of interoceptive performance and metacognitive measures will be analyzed descriptively and compared with (1) measures from a healthy control group and (2) end-of-treatment measures, using *t* tests or nonparametric tests, depending on data variability in the samples.

In substudy 3, the potential moderation of parental factors on treatment adherence (number of completed modules) and main measure (gastrointestinal symptoms) for children or adolescents will be investigated using negative binomial regression and linear mixed models, respectively, adjusting for baseline parental distress, illness worries, and illness behavior, respectively.

In addition, the potential effect of treatment on these parental factors and all other child or adolescent measures will be analyzed using linear mixed regression models.

An experienced statistician will provide statistical support for all analyses.

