## Results

Recruitment of participants began in June 2022. Substudy 1 is finalized and expected to be published in 2025. Recruitment for substudies 2 and 3 is ongoing. By November 2024, 45 children and 24 adolescents have been included. Due to a skewed distribution in referrals, with a predominance of referrals on children, we continue to include children and adolescents until we have reached 30 adolescents. Inclusion is expected to be completed by January 2025 and data collection in March 2025.

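### Completed modules is a count capped at 10, but the planned negative binomial regression ignores the cap and cannot represent variance below the mean; the cost depends on an unstated completion pattern and standard-error type.

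*Protocol article*

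**What the plan says.** The Data Analyses section of the protocol article states for substudy 3 that "treatment adherence (number of completed modules) and main measure (gastrointestinal symptoms) for children or adolescents will be investigated using negative binomial regression". The same sentence pairs the second outcome, symptoms, with a mixed model, so the negative binomial model is the one for adherence. The parental factors are baseline distress, illness worries and illness behavior.

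The upper limit of the count is in Design and Content of Treatment: the treatment "consists of 10 modules for children, adolescents, and parents of children (with a new module every week) and 5 modules for parents of adolescents". On the source of the outcome, Measures of Parental Factors and Child Treatment Effects (Substudy 3) says only that "the number of completed treatment modules will be obtained from the treatment web page after the end of treatment". No expected mean, variance, completion rate or dropout rate is given, and the standard-error estimator is not stated.

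The planned size follows from Study Design: "a total of 72 children and adolescents, along with a corresponding number of parents, will undergo ICBT". Sample Sizes explains that the treatment-impact analyses of substudy 2 are explorative and have no a priori power calculation, and continues: "The same concerns the last study on parental factors (substudy 3) as possible effect moderators".

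**The concern.** Negative binomial regression is built for counts with no ceiling whose variance exceeds the mean. Modules completed by a child or adolescent cannot exceed 10, and when most families finish, the variance of such a count is often below its mean. The model cannot represent that. Its dispersion parameter stops at zero, the fit becomes Poisson, and the model-based standard errors describe more variation than the data contain. The log link also permits fitted means above the number of modules that exist.

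Adherence is one of the two outcomes named for the moderation analysis of parental factors, and it is part of the study's third aim. With about 72 families there is little precision to spare. A conservative test could leave a real association between parental distress or worry and adherence undetected.

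**Working it through.** **Inputs.** Cap K = 10 (children, adolescents, parents of children) or 5 (parents of adolescents), from Design and Content of Treatment. n = 72, from Study Design. The completion distribution is not in the documents and is varied below. Two-sided α = 0.05 is assumed, since the document states .05 only for substudy 2. The plan gives no figure for this analysis, so there is none to reproduce.

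**Step 1: what the cap implies.** For a count y between 0 and 10 with mean m, y² ≤ 10y, so Var(y) ≤ 10m − m² = m(10 − m). The negative binomial variance is m + αm² with α ≥ 0, so it is never below m.
- At m = 9 the bound is 9 × 1 = 9, equal to the mean. For m ≥ 9 overdispersion is impossible.
- At m = 8 the bound is 8 × 2 = 16, twice the mean. Either under- or overdispersion is possible.
- With K = 5 the bound is m(5 − m), which is at most m once m ≥ 4.

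Below m = 9, then, the cap alone does not settle the matter; the shape of the distribution does.

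**Step 2: impossible values.** In the Poisson limit, P(more than 10 modules) is 18% at mean 8 and 29% at mean 9. With mean 9 and a rate ratio of 1.2 per SD, the fitted mean one SD up is 9 × 1.2 = 10.8 modules.

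**Step 3: size under assumed distributions.** Setup: n = 72, one standard-normal parental factor, 1000 runs per scenario. The negative binomial (NB) model was fitted by maximum likelihood with model-based SEs, using Poisson when the dispersion is on its zero boundary. The comparator is a logistic model for modules out of 10 with Pearson dispersion (quasi-binomial, QB). Power is for log-odds 0.5 per SD (scenarios without a tail) or 0.8 per SD on dropping out (scenarios with a tail). SE ratio is the mean model SE over the actual sampling SD, under the null.

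| Assumed completion | Mean | Var/mean | SE ratio, NB | Type I, NB | Power NB vs QB |
|---|---|---|---|---|---|
| No dropout tail | 9.5 | 0.05 | 4.5 | 0.000 | 0.00 vs 0.83 |
| No dropout tail | 9.0 | 0.10 | 3.2 | 0.000 | 0.07 vs 0.97 |
| No dropout tail | 8.0 | 0.20 | 2.2 | 0.000 | 0.80 vs 1.00 |
| 10% drop out at 0-6 modules | 9.0 | 0.52 | 1.36 | 0.009 | 0.31 vs 0.50 |
| 20% drop out at 0-6 | 8.4 | 0.98 | 1.09 | 0.032 | 0.64 vs 0.67 |
| 20% drop out at 0-4 | 8.2 | 1.24 | 1.08 | 0.032 | 0.68 vs 0.72 |
| 30% drop out at 0-6 | 7.7 | 1.40 | 1.04 | 0.037 | 0.72 vs 0.76 |
| 30% drop out at 0-4 | 7.4 | 1.79 | 1.12 | 0.026 | 0.69 vs 0.77 |
| 30% drop out at 0-2 | 7.1 | 2.30 | 1.31 | 0.014 | 0.64 vs 0.79 |

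With 40-50% dropouts the SE ratio was 1.16-1.21. QB type I error was 0.037-0.058 throughout. Beta-binomial completion with mean 8.0-9.2 gave NB SE ratios of 1.15-2.1.

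**Step 4: same standard-error type for both models.** The power column above mixes two differences: the model family and the SE estimator. With beta-binomial completion, odds ratio 0.67 per SD, n = 72 and 600 runs:

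| Mean, variance | NB, model SE | NB, robust SE | Fractional logit, robust SE |
|---|---|---|---|
| 8.84, 3.9 | 11% | 42% | 45% |
| 8.75, 2.2 | 6% | 70% | 71% |
| 7.97, 6.2 | 45% | 59% | 59% |

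In the first row the full gap is 45 − 11 = 34 points. Of that, 42 − 11 = 31 points come from the SE type and 3 from the model family. Under the null, type I error was 5-7% (NB robust) and 6-8% (fractional logit).

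**The case against.** A reader might infer that most families will finish near the cap, that the standard errors are therefore certain to be too wide, and that a null adherence finding would be uninformative. The documents do not support this. They give no completion distribution, and even with 68-78% of families at 9-10 modules, a tail of 20-30% early dropouts brings the variance up to or above the mean. The standard errors are then mostly only 4-12% too wide.

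It can also be said that the harm belongs to the standard errors and not to the model family. Step 4 bears this out: robust standard errors on the planned model recover nearly all the power. A condensed article may leave that choice to a fuller document that is not shown.

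Finally, the error is conservative and creates no false associations, the analysis is explorative, and fitted probabilities above 10 modules matter little when the question is association.

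All of this limits the size of the problem. What it does not answer is that the article names a specific model for an outcome it elsewhere caps, and that the completion pattern is unknown at planning. A model that suits any bounded count is the safer choice.

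**Conclusion.** The mismatch is certain; its cost is conditional. Negative binomial regression ignores a cap stated in the same document and cannot represent variance below the mean. If completion is high without a sizeable early-dropout tail, and if model-based standard errors are used, those errors will be about 1.2 to 2 times too wide or more, and tests of the parental factors will be conservative. With 20-30% early dropouts the loss is usually small (3-8 points of power in the runs shown), though it reached 15 points when all dropouts left within the first two modules. That associations will in fact be missed is not established. These sizes rest on assumed completion distributions, one predictor and 72 families. This is a worthwhile correction to an explorative analysis and does not threaten the study's main conclusions.

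**What to change.** Analyse modules completed out of those available with a beta-binomial or a fractional/quasi-binomial logistic model. Use x of 10 for children and adolescents. If parents' modules are analysed, use x of 10 for parents of children and x of 5 for parents of adolescents. State the standard-error type: dispersion-adjusted, or robust with a small-sample form such as HC3. Report odds ratios per SD of each baseline parental factor. Any power comparison of candidate models should give both the same standard-error type.

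The cost is a change of wording and of regression command, with no new data. The effect scale changes from rate ratios to odds ratios. Robust standard errors are slightly liberal at about 72 families (type I error 4.5-8% in simulation); HC3 or a beta-binomial likelihood reduces this.

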In line with this, cognitive behavioral therapy (CBT) is the treatment supported by the strongest evidence of effect [24-26], with its main focus on restructuring potential child symptom-related maladaptive cognitions, emotions, and behaviors, and often with parental involvement. Swedish studies have documented the efficacy of internet-delivered cognitive behavioral therapy (ICBT) aimed at children and adolescents with FAPDs and their parents [27-29]. The ICBT focuses especially on exposure exercises and parental management of their child or adolescent’s symptoms. By enabling the child or adolescent to manage symptoms in previously avoided situations and thereby minimizing the gastrointestinal-specific fear, the treatment reduces the proposed visceral hypersensitivity, which over time leads to fewer abdominal symptoms.

Still, a proportion of the young patients do not improve from ICBT as the number needed to treat has been reported to be around 4, meaning approximately 4 patients must receive the treatment for 1 additional patient to experience adequate symptom relief [27,29]. Therefore, a deeper understanding of the mechanisms of change and the potential influence of additional modifiable factors on the treatment effect is required to improve treatment effects even more.

In the current study, we will evaluate translated versions of the Swedish ICBT for children and adolescents with FAPDs in a Danish context. The treatments target both children (aged 8-12 years) and adolescents (aged 13-17 years) and their parents, which provides a unique possibility to examine both child or adolescent and parental factors before and after treatment. The aims of the study are to (1) investigate the detailed trajectory of the effect of ICBT in children and adolescents with FAPDs, (2) explore potential illness-related cognitive biases and interoceptive accuracy in children and adolescents with FAPDs compared with healthy controls, and if these factors are changed after ICBT, and (3) explore if parental distress, illness worries, and behaviors may impact the child or adolescent’s treatment adherence and outcome.

This protocol article is reported following the SPIRIT (Standard Protocol Items Recommendations for Interventional Trials) guidelines [30].

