## Discussion

### Principal Findings

With this study, we aim to explore previously sparsely investigated areas of ICBT for children and adolescents with FAPDs related to both child or adolescent and parental factors. This includes examining the detailed trajectory of effect, the presence of and potential changes in cognitive biases, and interoceptive inaccuracy after treatment, as well as investigating the potential role of parental distress, illness worries, and behavior as effect moderators.

Previous studies have demonstrated the effectiveness of Swedish ICBT programs in reducing abdominal symptoms and improving the quality of life in children and adolescents with FAPDs. Mediation analyses have shown that positive changes in symptom-specific avoidance behavior and fear mediate the treatment effects [17,18,27,29]. However, the detailed trajectory of treatment effects—specifically when and how possible changes occur during treatment for individual patients—remains unknown, and this will be investigated in substudy 1. This research could provide new insights into the mechanisms of change underlying treatment effects and could be clinically valuable for both therapists and patients.

To the best of our knowledge, this study is one of the first to assess cognitive biases and the ability to sense and interpret signals from the body (ie, interoception) in this patient group in comparison with healthy controls as well as to explore potential changes in these factors after treatment with CBT. Both factors are suggested to play a vital role in the predictive processing model, explaining the pathophysiology of FAPDs [11]. However, so far, they have mainly been studied in adults with various functional disorders [40,68-69,75-78]. By uncovering more knowledge about these factors, the results can potentially be used to further refine already established treatments. For example, this could involve adding biofeedback to train interoceptive accuracy or enhancing exposure exercises addressing specific cognitive biases that lead to fearful responses to gastro-related sensations and avoidance behavior.

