The study has some limitations. In substudy 1, the generalizability of SCED study results has traditionally been questioned due to the low number of participants. However, our study adheres to guidelines that include multiple data points across different phases, randomization of the length of the baseline phase, and replication across several participants, thereby optimizing generalizability. Furthermore, participants are expected to answer daily questions for an extended period, which could induce some fatigue in responding and potentially affect reliability. Still, the inclusion of several close data points increases precision in analyses and helps buffer against occasional data loss. In addition, the setup was tested on 4 prestudy patients, who reported that the daily questionnaire was easy and quick to answer.

In substudy 2, we use the BY-GIS task, which is newly developed and has not been previously tested in patients. However, the task is developed based on well-known paradigms and previous tests, and it has already been tested in a sample of 96 healthy age-matched controls with good usability [38]. The interoception HRD measures participants’ ability to sense their pulse, which is not directly related to gut sensations but falls within the broader perspective of interoception. However, studies in adults suggest altered interoceptive accuracy across different diagnoses of functional disorders and chronic pain, which indicates that there may be a general hypersensitivity to inner sensations in this patient group as well [86]. Since this study is one of the first to investigate interoceptive accuracy in children and adolescents with FAPDs, we believe it is still valuable to use this well-known and widely used interoception measure.

Substudy 3 is an open pilot trial without a control group for comparison which means conclusions regarding the clinical effect of the treatment should be interpreted with caution. However, the substudy is explorative and primarily aims to investigate new and additional modifiable treatment targets on a parental level.

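### Substudy 3 describes as effect moderation an analysis that, as worded, estimates association with symptom level, and a single-arm design can at most show prediction of change

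*Protocol article*

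**What the plan says.** The Data Analyses section sets the question for substudy 3 as "the potential moderation of parental factors on treatment adherence (number of completed modules) and main measure (gastrointestinal symptoms"), to be examined "using negative binomial regression and linear mixed models, respectively". The parental factors enter by "adjusting for baseline parental distress, illness worries, and illness behavior, respectively". No interaction with time is named.

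The moderator label recurs elsewhere. Sample Sizes gives no power calculation for treatment change in substudy 2 and then adds: "The same concerns the last study on parental factors (substudy 3) as possible effect moderators". Principal Findings announces "investigating the potential role of parental distress, illness worries, and behavior as effect moderators". The aim in the Introduction is worded differently, to "explore if parental distress, illness worries, and behaviors may impact the child or adolescent’s treatment adherence and outcome".

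On design, Study Design states that "a total of 72 children and adolescents, along with a corresponding number of parents, will undergo ICBT", and the limitations paragraph under Principal Findings says "Substudy 3 is an open pilot trial without a control group for comparison". That paragraph asks for caution about the clinical effect of treatment and then notes that the substudy is explorative and looks for modifiable parental targets. Table 2 lists gastrointestinal symptoms at T1 (baseline), T2, T3 and T4 (follow-up).

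**The concern.** There are two separate gaps between the stated question and what can be estimated.

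- **Model.** Moderation, in the protocol's own usage, concerns change: Principal Findings describes earlier work in adolescents with chronic pain in which high parental distress went with less improvement. In a repeated-measures model that is a time-by-factor term. Entering the factor as an adjustment covariate gives its average association with symptoms over the outcome visits, including pre-treatment T1 if T1 is one of them.
- **Design.** To say that a factor modifies the effect of ICBT, one must know how it relates to change without ICBT. With every patient treated, that is not observed.

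At stake is the purpose of the substudy, which is to find parental targets for improving treatment. A factor that merely goes with worse symptoms throughout could be reported as a moderator. A factor that does relate to change could be missed if its average association with level is near zero.

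**Working it through.** The article gives no numerical figure for substudy 3, so there is none to reproduce. The check sets the model against the question and then illustrates the size.

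**Step 1: what each model estimates.** Let *y* be the symptom score, *t* the visit and *P* the baseline parental factor.

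- Covariate model: *y* = time + β·*P* + patient effect + error. β is the association of *P* with level, the same at every visit. Nothing in the model lets change depend on *P*.
- Interaction model: *y* = time + β·*P* + γ·(time × *P*) + patient effect + error. γ is the difference in change per unit of *P*.
- In a single arm, γ = γ(natural course, including regression to the mean) + γ(treatment). Only the sum is estimable.

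**Step 2: how often the covariate would be significant when *P* has no link with change.** Inputs: n = 72 (planned total, Study Design), four visits (Table 2), two-sided α = .05. Assumed, not in the documents: correlation *r* = 0.2 to 0.4 between *P* and symptom level at each visit, and correlation 0.6 between visits.

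- One visit: power ≈ Φ(atanh(*r*)·√(n − 3) − 1.96), with √69 = 8.307.
- Mean of four visits: replace *r* by *r* / √((1 + 3 × 0.6)/4) = *r* / 0.837.

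| *r* | one visit: z, power | *r* with 4-visit mean | 4-visit mean: z, power |
|---|---|---|---|
| 0.2 | 1.68, 39% | 0.239 | 2.02, 53% |
| 0.3 | 2.57, 73% | 0.359 | 3.12, 88% |
| 0.4 | 3.52, 94% | 0.478 | 4.32, 99% |

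Under the same assumptions the interaction test rejects in 5%. That is simply its α, because no link with change was assumed.

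**Step 3: simulation of both models.** One arm, n = 72, T1 to T4, 300 replicates per scenario. Assumed: random-intercept SD 0.8, residual SD 0.6, effects of 0.4 per SD of *P*.

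| True situation | covariate model: *P* significant | interaction model: time × *P* significant |
|---|---|---|
| *P* affects level only | 94% | 5% |
| *P* alters change under treatment, average level effect zero | 6% | 98% |
| *P* alters change under treatment, baseline level effect zero | 53% | 98% |
| *P* alters only the untreated course | 51% | 98% |

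Rows 1 and 2 show the model gap: the covariate test responds to level and can be blind to change. Rows 3 and 4 show the design gap. In one arm they produce data of the same form, so the two rejection rates agree within simulation error (53% and 51%; 98% and 98%). No single-arm model can tell them apart.

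**Step 4: the adherence outcome.** Completed modules are a single count at the end of treatment, with no pre-treatment value and no meaning without treatment. A time-by-factor term does not apply. Regressing the count on baseline parental factors by negative binomial regression is a suitable analysis of what predicts adherence; only the word moderation does not fit.

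**The case against.** The strongest reply is that the Data Analyses text is one condensed sentence in a journal article. It names a purpose, a model family and the baseline factors, but no model formula, and it does not say whether T1 is an outcome visit. Interaction terms are commonly left to the SAP, which is not shown and may contain one. This stands in part: a reader might infer that the analysis will certainly contain main effects only, and the documents do not support that. What can be said is that the operation named, adjustment, does not by itself answer the question named. The percentages in Step 2 depend on that reading and on assumed correlations.

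Other points also stand:

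- The negative binomial model for modules is sound, so a reader should not take the whole substudy 3 analysis to be wrong.
- The aim and the Conclusion do not use the word moderator, and where it is used for this study it is hedged as possible or potential.
- Because Table 2 includes parent-reported gastrointestinal symptoms, a reader might infer that a distressed parent rating the child will drive the result. Self-report is collected too, nothing says that parent report is the analysed outcome, and the choice of rater is ordinary SAP detail.
- The substudy is openly explorative and unpowered, and the missing control group is disclosed.

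What the reply does not meet is the design gap. An SAP can add an interaction but not a control arm, and the stated caution reaches only the clinical effect, not the moderator claim that depends on the same missing comparison.

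**Conclusion.** The concern holds, with moderate severity. As worded, the mixed-model analysis of gastrointestinal symptoms estimates association with average symptom level. An unseen SAP could repair that part. Independently of any SAP, the single-arm design supports statements about prediction of change under treatment, not about moderation of the ICBT effect, so the label in Data Analyses, Sample Sizes and Principal Findings claims more than the design can give.

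The size is illustrative: about 39% to 94% (one visit) or 53% to 99% (four-visit mean) significant covariate results with no link to change, against 5% for the interaction. It rests on n = 72, *r* = 0.2 to 0.4, a between-visit correlation of 0.6 and a covariate-only model. Other values would move the percentages; the distinction between level and change, and between predictor and moderator, does not depend on them. The explorative status keeps this from being a critical fault, but it does not turn a level association into a test of moderation.

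**What to change.** - **Gastrointestinal symptoms:** state a linear mixed model with time, baseline parental factor and time-by-factor, and base the inference on the interaction at T3 (and T4).
- **Completed modules:** keep the negative binomial regression and describe it as prediction of adherence.
- **Wording:** in Data Analyses, Sample Sizes and Principal Findings, replace moderation and effect moderators by predictors of change or of adherence. The aim and the Conclusion do not use the term and need no replacement on this account.
- **Limitations:** extend the caution about the missing control group to these inferences, naming natural course and regression to the mean.

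The cost is a few sentences and a more modest conclusion. No new data are needed, since the T1 to T4 measurements are already planned.
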